#### Randomization

A biostatistician, blinded to screening and baseline assessment data, conducted computer-generated randomization on a 2:3 ratio (control:intervention) stratified based on clinical status (low risk—asymptomatic recovery; high risk—continued symptomatic, recovering, prodromal, and symptomatic recovery; Tables 4 and 5). Patients were randomized in permuted blocks of 5 at each site. The unbalanced design increases power to investigate effects within the intervention arm with minimal effect on the investigation of outcomes. Participants were stratified because time to relapse is likely to be significantly shorter for the high-risk participants who have not met the time or symptom number criteria for recovery from the last episode or who are recovered but have subsyndromal or prodromal symptoms [9,94,151,152]. Although many prior face-to-face psychotherapy studies restrict participant inclusion to those in asymptomatic recovery [10-15,18], this study includes additional high-risk individuals to increase access to the intervention.

**Table 4 table4:** Clinical status when in an episode.

DSM 4 episode criteria	Episode entry criteria^a^ met?	Number of moderate symptoms of	Impairment	Consecutive days	PSR^b^
Mania	Yes	Mania≥3 if elevated Mania≥4 if only irritable	≥Moderate or hospitalized or psychosis	≥7 or hospitalized	5-6
Depression	Yes	Depression≥5	≥Moderate	≥10 out of 14	5-6
Mixed^c^	Yes, for both mania and depression	Criteria for both mania and depression	≥Moderate	≥7	5-6
Hypomania	Yes	Mania≥3 if elevated Mania≥4 if only irritable	< Moderate and not hospitalized and no psychosis	≥4	3

^a^Entry criteria: mania—moderate severity elevated, expansive, or irritable mood ≥ 7 consecutive days; depression—moderate severity depressed mood or loss of interest/pleasure ≥ 10 out of 14 consecutive days; hypomania—moderate severity elevated, expansive, or irritable mood ≥ 4 consecutive days and < 7 consecutive days. Clinical Monitoring Form symptom severity scale: none=0, mild=0.5, moderate=1, marked=1.5, and severe=2.

^b^PSR: Psychiatric Status Rating score.

^c^Mania with concurrent depression for 1 week. Count depressive symptoms for 5/7 consecutive days instead of 10/14.

**Table 5 table5:** Clinical status when not in an episode.

Clinical Monitoring Form criteria	Recovered from last acute episode?	Symptom count^a^ and impairment	PSR^b^
Continued symptomatic	No	Symptom count>2 or ≥ moderate impairment	3-4

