#### Outcome Assessments

The primary outcome, time to relapse, will be measured as the number of weeks to episode onset (depression, mania, hypomania, or mixed) based on the Diagnostic and Statistical Manual of Mental Disorders fourth edition (DSM-4) criteria. The DSM-4 episode criteria were chosen to allow comparison with prior RCTs of face-to-face psychotherapy for bipolar disorder, as these studies primarily used the DSM-4 episode criteria [10-18]. To determine the number of weeks to episode onset, weekly clinical status ratings (Tables 4 and 5) were assessed by timeline follow-back rating of bipolar disorder symptom severity (Multimedia Appendix 7) using a modified Longitudinal Interval Follow-Up Evaluation (LIFE) and Clinical Monitoring Form (CMF) [148,149,153]. The secondary outcomes include the percentage of time symptomatic, symptom severity, and QOL. To determine percentage of time symptomatic, weekly psychiatric status ratings (Table 6) were assessed using the LIFE-CMF to determine the percentage of time symptomatic. A week will be scored as symptomatic if the psychiatric status rating is greater than one and a half (Table 6). Symptom severity was assessed using the Quick Inventory of Depressive Symptomatology (QIDS)–Clinician Rating and the Young Mania Rating Scale [154-157]. QOL was assessed using the World Health Organization Quality of Life BREF [158].

**Table 6 table6:** Psychiatric status rating.

Score	Rating	Definition
6	Severe episode	Psychotic symptoms or severe impairment
5	Episode	No psychotic symptoms and no severe impairment
4	Marked symptoms	Symptom count^a^ >2 and marked or severe impairment
3	Moderate symptoms	Symptom count >2 or moderate impairment
2	Residual or prodromal symptoms	Symptom count >0 and ≤2. No moderate, marked, or severe impairment
1.5	Mild symptoms	≥One mild symptom. No moderate, marked, or severe symptoms (Symptom count=0). No moderate, marked, or severe impairment
1	No symptoms	No mild, moderate, marked, or severe symptoms. No impairment

^a^Symptom count: Sum of symptom severity, if |severity| ≥1 round up, otherwise 0. Clinical Monitoring Form symptom severity scale: none=0, mild=0.5, moderate=1, marked=1.5, and severe=2.

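### Table 4 and its footnote a give incompatible duration rules for hypomania and for hospitalized mania, so the primary relapse event has two definitions

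*Protocol article*

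**What the plan says.** Outcome Assessments defines the primary outcome: "time to relapse, will be measured as the number of weeks to episode onset (depression, mania, hypomania, or mixed"), based on DSM-4 criteria. It also says how the outcome is obtained: "To determine the number of weeks to episode onset, weekly clinical status ratings (Tables 4 and 5) were assessed by timeline follow-back rating". Tables 4 and 5, in the Randomization section, are therefore the event definition.

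Table 4 has a column headed "Episode entry criteria^a^ met", and every row answers Yes. Footnote a supplies the criteria:

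- Mania: "mania—moderate severity elevated, expansive, or irritable mood ≥ 7 consecutive days".
- Hypomania: "hypomania—moderate severity elevated, expansive, or irritable mood ≥ 4 consecutive days and < 7 consecutive days".

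The rows have their own duration and impairment columns:

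- The mania row gives duration as "≥7 or hospitalized" and requires at least moderate impairment, hospitalization or psychosis.
- The hypomania row gives duration as at least 4 days, uncapped, and impairment as "< Moderate and not hospitalized and no psychosis".

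**The concern.** A row and its entry criterion should agree, because a week must satisfy both to be an episode. Here they disagree twice. The footnote caps hypomania below 7 days where the row does not, and it removes the hospitalization route to the mania duration that the row allows.

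Two people applying the printed rules to the same ratings, one guided by the rows and one by the footnote, could reach different relapse counts and different relapse weeks. The footnote version is also not monotone: a hypomania of a given severity is an episode at 5 days and not at 9.

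The same clinical statuses define the randomization strata. They may also define the current mood episode that excludes a person from entry, although the article does not say so. The Objective says the description is meant to support replication, so the printed rule has to be one that can be applied.

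**Working it through.** The article states no figure to reproduce here; this is a check of logic.

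**Inputs.** Table 4 rows for mania and hypomania, footnote a, Table 5, Table 6. The symptom-number condition is taken as met (3 or more moderate symptoms, or 4 or more if mood is only irritable).

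**Rules as coded.** d = days of mood disturbance.

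- Mania row: (at least moderate impairment, or hospitalized, or psychosis) and (d ≥ 7 or hospitalized).
- Hypomania row: below-moderate impairment, not hospitalized, no psychosis, and d ≥ 4.
- Footnote entry: mania d ≥ 7; hypomania 4 ≤ d < 7.

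**Readings compared.**

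- A: each row needs its own footnote criterion.
- B: rows only, footnote ignored.
- C: Yes is satisfied by either the mania or the hypomania entry criterion.

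**Grid.** d from 1 to 10, by impairment (2 levels), hospitalization (2) and psychosis (2): 10 × 2 × 2 × 2 = 80 combinations. These are logical cases, not patients.

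| Presentation | A | B | C |
|---|---|---|---|
| d 7–10, below-moderate impairment, not hospitalized, no psychosis (4 cases) | no episode | hypomania | hypomania |
| Hospitalized, d 4–6 (3 × 2 × 2 = 12 cases) | no episode | mania | mania |
| Hospitalized, d 1–3 (3 × 2 × 2 = 12 cases) | no episode | mania | no episode |

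A and B differ in these 4 + 12 + 12 = 28 cases and nowhere else. C still differs from B in 12.

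**Group 1, example.** Ten days of elevated mood, three moderate symptoms, mild impairment, no admission, no psychosis. The mania row fails on impairment. The hypomania row is met, but its entry criterion fails because 10 is not below 7. At five days the same picture passes both parts and is a hypomanic episode.

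**Group 2, example.** Five days of manic mood in total, with admission. The mania row is met through hospitalization, but entry fails because 5 is below 7. The hypomania row fails because the patient was hospitalized.

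**Where these weeks go.** Three moderate symptoms give a symptom count of at least 3 × 1 = 3, which exceeds 2. Table 5 then gives prodromal if the participant had recovered from the last episode, or continued symptomatic if not. Neither is an episode, so neither is a relapse.

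**Percentage time symptomatic.** Table 6 rates a non-episode week with a symptom count above 2 at 3 or 4. The symptomatic threshold is a rating above 1.5, so the week counts as symptomatic under either rule.

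**The case against.** The strongest reply is that this may be a condensed footnote and nothing more. The rating procedure is referred to Multimedia Appendix 7, onset is tied to DSM-4, and assessors may have coded correctly throughout. The entry column could also be read as satisfied by either manic-pole criterion, which would make long hypomania an episode.

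Part of this stands. How weeks were actually coded is unknown, so it does not follow that such episodes were in fact left out. But the looser reading is the less natural one, because the mixed row specifies which entry criteria it needs, and it still leaves hospitalized mania of 1 to 3 days outside every row. The article prints two rules that disagree; this is not detail left to an appendix.

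Three stronger inferences are tempting and are not supported:

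- **That any mania admitted before day 7 is lost.** The footnote counts days of mood disturbance and does not stop at admission. A patient admitted on day 3 who remains manic to day 7 meets entry. Only disturbances totaling fewer than 7 days are affected.
- **That the hazard ratio is biased against LiveWell.** This would need the intervention to shorten hypomanias from 7 or more days into the 4-to-6-day range. Nothing in the article shows that. Assessors were blinded and the rule is common to both arms.
- **That a particular amount of power is lost.** The article gives no share of relapses of these kinds, and a participant with an uncounted episode may have a later qualifying one, which delays the event and does not remove it.

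**Conclusion.** The contradiction is real and lies within the definition of the primary event. Under the row-specific reading, exactly two groups meet a row's own duration and impairment conditions but are not episodes: hypomania of 7 or more days with below-moderate impairment, no hospitalization and no psychosis; and hospitalized manic presentations with fewer than 7 days of mood disturbance in total.

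The number of relapses affected cannot be determined from the article and could be zero if coding followed the rows. The direction of any bias is likewise undetermined.

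The conclusion assumes that Yes in a row refers to that row's own entry criterion and that the symptom-number condition is met. It does not depend on which rule is clinically right, which is not judged here. It still needs correcting, because the rule generates the primary outcome and the remedy is cheap.

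**What to change.** 1. Reconcile footnote a with the Table 4 rows, for both hypomania and mania, against the DSM-4 criteria that Outcome Assessments names. While doing so, state how a disturbance of 4 to 6 days with at least moderate impairment and no hospitalization is classified; it fails both rows under every reading above.
2. State which rule generated the recorded weekly statuses. If it already agrees with the reconciled rule, correcting the text is enough.
3. If coding followed the footnote and the reconciled rule differs, re-derive clinical status and relapse week blinded to arm, wherever the stored ratings hold the needed duration data (the article does not say whether they do). Do this before the arm comparison if that is still possible. The Intervention Evaluation overview says analysis is underway, so otherwise report it as a sensitivity analysis.
4. Report how many relapse events, relapse weeks and baseline strata change. Strata could change because an added episode can alter whether a participant counts as recovered. Keep the strata as randomized in the analysis.

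The cost is a text correction and, at most, a small amount of recoding. The downside is that some recorded statuses may change.

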#### Outcome Assessments

The primary outcome, time to relapse, will be measured as the number of weeks to episode onset (depression, mania, hypomania, or mixed) based on the Diagnostic and Statistical Manual of Mental Disorders fourth edition (DSM-4) criteria. The DSM-4 episode criteria were chosen to allow comparison with prior RCTs of face-to-face psychotherapy for bipolar disorder, as these studies primarily used the DSM-4 episode criteria [10-18]. To determine the number of weeks to episode onset, weekly clinical status ratings (Tables 4 and 5) were assessed by timeline follow-back rating of bipolar disorder symptom severity (Multimedia Appendix 7) using a modified Longitudinal Interval Follow-Up Evaluation (LIFE) and Clinical Monitoring Form (CMF) [148,149,153]. The secondary outcomes include the percentage of time symptomatic, symptom severity, and QOL. To determine percentage of time symptomatic, weekly psychiatric status ratings (Table 6) were assessed using the LIFE-CMF to determine the percentage of time symptomatic. A week will be scored as symptomatic if the psychiatric status rating is greater than one and a half (Table 6). Symptom severity was assessed using the Quick Inventory of Depressive Symptomatology (QIDS)–Clinician Rating and the Young Mania Rating Scale [154-157]. QOL was assessed using the World Health Organization Quality of Life BREF [158].

**Table 6 table6:** Psychiatric status rating.

Score	Rating	Definition
6	Severe episode	Psychotic symptoms or severe impairment
5	Episode	No psychotic symptoms and no severe impairment
4	Marked symptoms	Symptom count^a^ >2 and marked or severe impairment
3	Moderate symptoms	Symptom count >2 or moderate impairment
2	Residual or prodromal symptoms	Symptom count >0 and ≤2. No moderate, marked, or severe impairment
1.5	Mild symptoms	≥One mild symptom. No moderate, marked, or severe symptoms (Symptom count=0). No moderate, marked, or severe impairment
1	No symptoms	No mild, moderate, marked, or severe symptoms. No impairment

^a^Symptom count: Sum of symptom severity, if |severity| ≥1 round up, otherwise 0. Clinical Monitoring Form symptom severity scale: none=0, mild=0.5, moderate=1, marked=1.5, and severe=2.

#### Target Assessments

The targets selected for assessment were taking medications as prescribed, obtaining adequate sleep duration, maintaining regular routines, and managing signs and symptoms as these targets are readily amenable to monitoring using the Daily Check-In, which is a core feature of LiveWell. Medication adherence was assessed using the Tablet Routine Questionnaire [159-161] and focused on percentage adherence with prescribed psychiatric medications, not including those prescribed as needed. Sleep duration, quality, and excessive sleepiness were assessed using the CMF, QIDS, Pittsburgh Sleep Quality Index, and an additional question to capture excessive sleepiness [162-164]. Sleep duration was primarily considered in this study. Sleep quality and excessive sleepiness will be explored secondarily because interepisode insomnia and hypersomnia are risk factors for relapse [107,163,165,166]. Routine was assessed using a 5-question trait version of the Social Rhythm Metric [167-170] and will be assessed primarily by a frequency score (Multimedia Appendix 7). Finally, the management of residual and prodromal signs and symptoms was assessed using the Symptom Management Scale. This scale was developed from the prodromes coping interview and inventory, which has been used in face-to-face cognitive behavioral therapy for bipolar disorder [99,137,142,171]. The outcome measure will be the total coping score (Multimedia Appendix 7).

#### Outcome and Target Assessment Delivery

Assessors blinded to the study arm conducted outcome and target assessments by telephone at baseline and then every 8 weeks until study exit at week 48 (Figure 6). Windows for complete assessments were up to 4 weeks after the assessment due date, calculated from the baseline assessment date. To minimize assessment burden and because QOL may vary less rapidly than other outcomes [172], the QOL assessment was delivered only at 0, 24, and 48 weeks. Assessments began by focusing on participants’ experiences over the prior 2 weeks. Mood and sleep were assessed using combined mood (CMF, QIDS, and Young Mania Rating Scale) and combined sleep (CMF, QIDS, and Pittsburgh Sleep Quality Index) instruments (Multimedia Appendix 7). The combined instruments streamlined the interviews and reduced the time required to complete the assessments. This was followed by assessment during the prior 2 weeks of routine (Social Rhythm Metric), medication adherence (Tablet Routine Questionnaire), and depending on the week QOL.

Information from the assessment of the prior 2 weeks was then used to anchor the timeline follow-back of weekly depressive and manic symptom severity (LIFE-CMF). In addition to assessing symptom severity, timeline follow-back using the LIFE assessed weekly variations in anxiety, suicidal ideation and attempts, psychotic symptoms, substance use, life events [173], mental health treatment attendance, and psychiatric medication adherence (Multimedia Appendix 7). The Symptom Management Scale was assessed last because it did not focus on experiences during the previous 2 weeks or since the last assessment. Instead, participants were asked to imagine experiencing ongoing or new low-level depressive or manic symptoms and how they might manage them (Multimedia Appendix 7). This approach was used because participant clinical status during the assessment interval may not have required management of prodromal or residual symptoms.

#### Determinant Assessments

To assess changes in the determinants proposed to govern the enactment of target behaviors, determinant questionnaires were developed for each assessed target (Multimedia Appendix 8). The determinant questionnaires are derived from the question stems of existing medication adherence questionnaires for schizophrenia and bipolar disorder [174,175] and health psychology questionnaires for assessing determinants of physical exercise and other health-related behaviors [76,77,176-183]. The questionnaires measure determinants proposed to underlie the pursuit of LiveWell’s four assessed behavioral targets (taking medications as prescribed, obtaining adequate sleep duration, maintaining regular routines, and managing signs and symptoms). The questionnaires were delivered via a web survey sent by the coaches to the participants. For the intervention arm, they were delivered at weeks 0, 16, and 48 (Figure 6). For participants in the control arm, they were only delivered at week 48 (Figure 6) because the delivery of the determinant questionnaires may serve as an active intervention [76,77,181]. Eventually, the determinant questionnaires may be incorporated into the smartphone app to provide real-time assessment of target change processes to facilitate improved adaptive real-time feedback.

#### Behavioral Sensing

Participants were offered the option of having the LiveWell app (intervention arm only) and an app for sensor data collection and secure transmission of data (Purple Robot, intervention, and control arms) [184] installed on their smartphone. Alternatively, participants had the option of receiving the apps on a study phone with an unlimited national calling and data plan. Individuals who opted to use their own phone were reimbursed for their plan up to the cost of the study phone plan or their own plan, whichever was less. All participants were provided with a wrist-worn actimeter (Pebble). Participants were asked to (1) use the phone with the apps as their only phone, (2) carry the phone with them whenever they left home, and (3) wear the watch 24 hours a day, 7 days a week except while it was charging.

#### Assessor Fidelity Assessments

Clinical outcomes and target assessments were performed by assessors with master’s degrees in mental health or counseling. Structured interviews can be validly and reliably administered by such personnel [185-189]. Assessors were trained by mental health professionals (a psychiatrist and psychologist) with instruction and practice on audiotaped ratings, followed by observing, role-playing, and observed assessments (≥3 each). All assessment telephone calls were audiotaped. Assessor fidelity focused on using the CMF for assessing status in the prior 2 weeks. Assessment audiotapes were randomly selected each month (15%) for review and scoring by a trained mental health professional (psychologist) to assess the fidelity of CMF scoring for symptom severity (percent match within 0.5), asymptomatic status (percent match), clinical status (percent match), and psychiatric status rating (percent match).

#### Analysis Overview

As the randomization was stratified by risk group, analyses will examine if an interaction between risk strata and the study arm is present. If no evidence of an interaction is evident, the models will be stratified or adjusted for risk strata. For time to relapse, missing data for participants who dropped out or were lost to follow-up will be censored at their last study visit. Percentage time symptomatic will be calculated based only on the observed time in the study. For longitudinal data (symptom severity, QOL, targets), multiple imputation using Markov Chain Monte Carlo methods will be used to address missing data by creating five unique data sets (SAS procedure PROC MI), and the results will be combined (SAS procedure PROC MIANALYZE) to obtain valid statistical inferences and least square means of the outcomes for each time point data will be calculated.

#### Aim 1: Primary and Secondary Outcomes Analysis

Time-to-relapse curves will be constructed using the Kaplan-Meier method. Log-rank tests will be used to determine if there is a univariate impact of the study arm while adjusting for risk strata. Cox proportional hazard models will then be fit to adjust for risk strata. Proportional hazards assumptions will be assessed, and the estimated hazard ratio and CIs will be presented. To compare percent time symptomatic, linear regression models will be used to determine if there was an interaction between risk strata and the study arm. If no evidence of interaction is seen, the main effect of arm will be reported and least square means will be estimated while adjusting for risk strata. Generalized linear mixed models for longitudinal data will be used for symptom severity and QOL measures. We will examine the interactive effects of the intervention on time. If no interaction is detected, we will test the independent effects of time as well as the treatment group.

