Adjunctive psychotherapy interventions for bipolar disorder typically enroll individuals who are between acute episodes and focus on the prevention of relapse [10-15,18]. Time to episode recurrence was thus selected as the primary clinical outcome (Figure 1) to ensure that the efficacy of LiveWell can be assessed in the context of existing face-to-face studies. As cumulative measures of symptom burden are better predictors of psychosocial functioning than episode recurrence rate [94], percentage time symptomatic and symptom severity were selected as secondary outcomes. QOL was also chosen as a secondary outcome because the absence of symptoms is not synonymous with QOL, and improvement in QOL is highly valued by individuals with bipolar disorder [39,95,96].

Although empirically supported adjunctive therapies for bipolar disorder use diverse approaches, changes in shared behavioral targets may result in the improved outcomes produced by these therapies [5,18,26,33,97,98]. Thus, the LiveWell intervention seeks to improve clinical and recovery outcomes by assisting individuals with managing targets proposed to underlie the impact of existing face-to-face therapies (Figure 1). LiveWell emphasizes the importance of identifying signs and symptoms of relapse, developing plans and monitoring for relapse, and enacting and adjusting plans as needed (managing signs and symptoms) [99,100]. In addition, LiveWell uses a similar process to support taking medications as prescribed [101-105], obtaining adequate sleep duration [106-110], and maintaining regular routines [111-115]. LiveWell also addresses strengthening social support [5,35], managing stressors [33,35], and engaging in healthy habits regarding diet, exercise, and substance use [5,116-118].

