Prodromal	Yes	Symptom count>2 or new^c^ or ≥ moderate impairment	2-4
Recovering	No, recovering ≤8 consecutive weeks	Symptom count≤2 and < moderate impairment	1-2
Symptomatic recovery	Yes	Symptom count>0 and ≤2 and < moderate impairment	2
Asymptomatic recovery	Yes	Symptom count=0 and < moderate impairment	<2

^a^Symptom count: sum of symptom severity, if |severity| ≥1 round up, otherwise 0. Clinical Monitoring Form symptom severity scale: none=0, mild=0.5, moderate=1, marked=1.5, and severe=2.

^b^PSR: Psychiatric Status Rating score.

^c^Two new moderate, marked, or severe symptoms developed while in recovery.

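### The high-risk label pools four prognostically different statuses, and the Cox and percent-time models adjust only for that label, so baseline information already collected goes unused

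*Protocol article*

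**What the plan says.** All references are to the Protocol article.

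- **Strata (Randomization).** The two levels are "low risk—asymptomatic recovery; high risk—continued symptomatic, recovering, prodromal, and symptomatic recovery". Stratification is justified by an expected shorter time to relapse in "high-risk participants who have not met the time or symptom number criteria for recovery from the last episode or who are recovered but" still have subsyndromal or prodromal symptoms.
- **Statuses (Table 5, Randomization).** Two of the four high-risk statuses are not recovered from the last acute episode: continued symptomatic (psychiatric status rating 3-4) and recovering (rating 1-2, entered as "No, recovering ≤8 consecutive weeks"). The other two are recovered: prodromal (2-4) and symptomatic recovery (2).
- **Models (Aim 1: Primary and Secondary Outcomes Analysis).** The log-rank test is adjusted for risk strata, and then "Cox proportional hazard models will then be fit to adjust for risk strata". The linear regression for percentage time symptomatic also adjusts for risk strata.
- **Interaction (Analysis Overview).** The plan says that "analyses will examine if an interaction between risk strata and the study arm is present"; if no interaction is evident, models are stratified or adjusted for risk strata.
- **Context.** Intervention Framework says the outcome was chosen "to ensure that the efficacy of LiveWell can be assessed in the context of existing face-to-face studies". Randomization adds: "Although many prior face-to-face psychotherapy studies restrict participant inclusion to those in asymptomatic recovery", this trial takes in high-risk people as well, in order to widen access.

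**The concern.** The plan treats recovery and residual symptoms as prognostic, then reduces them to one binary label. Inside the high-risk half of that label the rating runs from 1 to 4, so someone with no symptoms who is a few weeks out of an episode shares a stratum with someone who has marked symptoms and impairment. Clinical status and rating are established for everyone at baseline, so finer adjustment needs no new data.

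Three things are at stake. Strong prognostic differences left inside a stratum pull a Cox hazard ratio toward 1 and cost power. Chance imbalance between arms in baseline symptoms stays uncorrected. For percentage time symptomatic, the omitted variable is the outcome's own starting value. There is also a reporting point: the stratum that matches many face-to-face trials is the low-risk one, and the article does not commit to showing its estimate.

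**Working it through.** **1. The plan's own figures.** Relapse of 60% versus 43% gives HR = ln(0.57)/ln(0.40) = 0.613, which agrees with the stated 0.61. At two-sided 5% and 2:3 allocation (0.4 × 0.6 = 0.24), 80% power needs (1.96 + 0.84)² / (0.24 × (ln 0.61)²) ≈ 134 events. With N = 200, 12% loss, 30 months of accrual and 12 more months of follow-up for everyone, about 135.6 events are expected and power is 80.5%, so the stated 80% is reproduced. With 12 months per person the count is about 94 and power is 65.1%. Individual exit is at week 48, so most of any gap below 80% comes from follow-up length and has nothing to do with pooling. Only the difference between the two models counts below.

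**2. Effect of the two-level label on the Cox model.** Inputs from the article: 205 participants, 2:3 allocation, exit at week 48, 12% loss, control relapse 60% at one year, HR 0.61. Assumed, because the article does not give them:

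- the low-risk share is 50%;
- half of the high-risk stratum is near-episode;
- other high-risk people have 1 to 2 times the low-risk hazard;
- near-episode people have 2 to 4 times the hazard of other high-risk people;
- HR 0.61 holds within every status.

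Method: solve the large-sample score equation of the Cox model stratified on high/low, then take power = Φ(|ln HR| × √(0.24 × events) − 1.96).

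| Other high-risk vs low-risk hazard | Near-episode vs other high-risk hazard | Strata-only HR | Events | Power, strata only | Power, status in model | Loss |
|---|---|---|---|---|---|---|
| 1 | 2 | 0.617 | 92.1 | 62.2% | 64.2% | 2.0 |
| 1.5 | 3 | 0.635 | 95.2 | 58.4% | 65.6% | 7.3 |
| 2 | 4 | 0.657 | 98.5 | 53.3% | 67.1% | 13.8 |

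A low-risk share of 30% or 40% raises the largest loss by less than one point. A simulation under similar assumptions gave strata-only HRs of 0.62, 0.63 and 0.65 for two-, three- and fourfold hazards, and gains of 2 to 12 points when status was added. Splitting the stratum by recovery status instead, with 1.5- to threefold hazards and 12-month follow-up, gave 0.612 to 0.641 and losses of about 1 to 9 points.

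**3. If the effect differs by status.** Keep HR 0.61 in recovered people, give recovered high-risk people 1.5 times the low-risk hazard, and double that for people not recovered. Let the low-risk share be 30-50% and the not-recovered share of the high-risk stratum 30-70%. An HR of 1.0 in people not recovered gives a pooled HR of 0.68-0.84; an HR of 0.8 gives 0.65-0.73; an HR of 0.5 gives 0.55-0.59. The direction is not fixed.

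**4. Percentage time symptomatic.** Outcome Assessments scores a week as symptomatic when the rating exceeds 1.5. By Table 5, continued symptomatic, prodromal and symptomatic-recovery participants are above that line at baseline, recovering participants (1-2) may be on either side, and asymptomatic-recovery participants (below 2) are at 1 or 1.5. The high/low label blurs this starting value. The article gives no correlation between baseline rating and outcome, so the gain cannot be sized.

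**5. Precision of a low-risk estimate.** The factor for the 95% limits is exp(1.96/√(0.24 × events)). If 60 to 100 low-risk people yield 27 to 45 events (assumed), the factor is 2.16 to 1.82. Around 0.61 that means about 0.28 to 1.32, or 0.34 to 1.11. The assumed 45% event share is close to the whole-trial 94/200 = 47%; later relapse in this stratum would widen the limits.

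**6. Reach of the interaction check.** With about 94 events split evenly between strata (assumed), the interaction log-HR has a standard error of √(2/(47 × 0.24)) = 0.42. For 80% power the two strata's HRs must differ by exp(2.80 × 0.421) ≈ 3.25-fold. The check also cannot see differences inside the high-risk stratum.

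**The case against.** The strongest reply is that nothing here is invalid. Randomization protects the comparison, and the stratified hazard ratio is a legitimate average for the people enrolled. That stands. So does the point that 0.61 in the sample-size section is a whole-population ratio, so a shift from it is no error in itself; what matters is how the two models compare on the same data. The calculated gain is also a best case, because the model is given the very indicator that generated the hazards.

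A reader might infer more than the article supports:

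- **That the primary hazard ratio is diluted as a matter of fact.** With a common effect the shift is small, and with differing effects it can go the other way (step 3).
- **That adjusting for status would separate continuation of the index episode from new recurrence.** It would not. The endpoint and the enrolled mix stay the same, a current mood episode is an exclusion rechecked at the baseline assessment, and the rating ranges of recovered and not-recovered statuses overlap.
- **That the trial promises a population-matched comparison with face-to-face studies.** It says the outcome was chosen so that efficacy can be read in their context, and it openly states that many, not all, of them had narrower entry.
- **That the low-risk estimate will be withheld unless an interaction appears.** The article does not say so; it simply makes no commitment to report it.

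It can also be said that covariates are often left to the analysis plan. Here, however, the article names the adjustment for both outcomes, and that stated choice is what can be improved.

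**Conclusion.** The point holds as one of efficiency and reporting. The plan regards status as prognostic, collects it for everyone, and uses only a two-level summary of it in the primary Cox model and the percent-time regression. Under a common HR of 0.61 and assumed two- to fourfold hazard differences within the high-risk stratum, the strata-only HR is about 0.62-0.66, and power is about 2 to 14 points below that of a model including status. The size rests entirely on assumed shares and hazards; if they are mild, the loss is negligible. The randomized hazard ratio is valid for the enrolled mix, and the documents do not establish that it is diluted or that it fails a promised comparison. The change is worth making because it is nearly free, not because the planned analysis is wrong.

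**What to change.** - Keep the randomization strata in all models.
- Add the baseline clinical status of Table 5 to the Cox model. Low risk is a single status, so this costs three degrees of freedom beyond the strata.
- Add the baseline psychiatric status rating to the percent-time-symptomatic regression, at one degree of freedom if entered linearly.
- The Overview of Intervention Evaluation says data analysis is underway. If unblinded data have already been seen, keep the stated models as primary and label these supportive.
- Whatever the interaction test shows, report the low-risk (asymptomatic recovery) Kaplan-Meier curve and hazard ratio with its confidence interval, descriptively, as context for face-to-face trials that enrolled only that population. State that it is imprecise.

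No new data are needed. The costs are a few model degrees of freedom and one extra estimate with wide limits.
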